## Methods

### Study design and participants

In this randomized, controlled, parallel-group superiority trial, we compare the effects of the IF diet to the usual diet on clinical symptoms, inflammation, and oxidative stress in overweight and obese postmenopausal women who suffer from RA with the diagnosis of a rheumatologist and by the criteria of the American College of Rheumatology (ACR) over 8 weeks, with a 1:1 allocation ratio, in 2023–2024. This study will be conducted on eligible patients who will be referred to the rheumatology clinics of the Tehran University of Medical Sciences. Participants will be randomly allocated into a control group with the usual diet, and an intervention group with the IF diet. The protocol of this study was approved by the Ethics Committee of Tehran University of Medical Sciences (IR.TUMS.IKHC.REC.1401.376) and was registered at the Iranian Registry of Clinical Trials (IRCT20230217057441N1). After explaining the objectives of the study and the method of its implementation, documented informed assent is obtained from the attendees (Fig. 1).

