#### Secondary outcomes

Secondary outcomes are the changes in erythrocyte sedimentation rate (ESR), C-reactive protein (CRP), disease activity score in 28 joints (DAS-28), Visual Analogue Scale pain intensity (VAS-pain), level of total oxidant and antioxidant capacity (TOC and TAC), oxidative stress index (OSI), tender joint count (TJC), swollen joint count (SJC), tender-swollen joint count difference (TSJD), morning stiffness count (MS), patient global assessment of disease activity (PGA), global assessment of disease activity (EGA), and clinical disease activity index (CDAI) from baseline values.

We will evaluate both primary and secondary outcomes two times, first after the run-in period, at the beginning of the intervention, and second, 8 weeks later.

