### Assessment of inflammation and pain

VAS-pain questionnaire will be used to evaluate the pain level in patients. This tool is widely employed to assess pain levels, in which the patient is asked to rate the intensity of pain experienced measured on a 100-mm horizontal line with anchor-like descriptors in the pain field including “no pain” and mark the “worst imaginable pain” on two lines, and then measure it from the left edge (= VAS score) [45]. CDAI will be used to evaluate inflammation in these patients. To measure this index, the total scores of four criteria TJC28, SJC28, and PGA with a scale of 0 to 10 cm including “very good” and “very bad” along two horizontal lines and overall disease activity assessment (EGA) with a scale of 0 to 10 cm including “very good” and “very bad” along two horizontal lines will be calculated. Finally, the points will be classified as below [46]:

≤ 2.8 disease recovery

> 2.8 to 10 low disease activity

> 10 to 22 moderate disease activity

> 22 high disease activity

DAS-28 criterion will be used to evaluate the level of disease activity in patients. DAS28 score will be counted using TJC28, SJC28, CRP, and VAS disease activity (0–100 mm) of the patient. The following mathematical formula is used to calculate the overall score:$$\textrm{DAS}28\textrm{- CRP}={0.56}^{\ast }\ \left(\textrm{TJC}28\right)+{0.28}^{\ast}\left(\textrm{SJC}28\right)+{0.36}^{\ast}\ln \left(\textrm{CRP}+1\right)+{0.014}^{\ast}\textrm{VAS}+0.96$$

DAS28 score can vary from 0 to 9.4 and its interpretation is according to the following data [47]:

> 5.1: High disease activity

Between 3.2 and 5.1: moderate disease activity

Between 2.6 and 3.2: low disease activity

< 2.6: disease recovery

CDAI and DAS-28 criteria have been proposed in the latest update of the American Rheumatology Association in 2019 as valid and reliable criteria for an evaluation of RA patients [48].

To evaluate the duration of morning joint stiffness, the morning stiffness duration questionnaires and the degree of stiffness perceived by the patient will be used. Morning stiffness duration questionnaires will include options of less than 15 min, less than 30 min, less than 60 min, less than 90 min, and more than 90 min. The degree of perceived stiffness will also be determined by choosing on a scale of 0 to 10 cm, including “no stiffness” and “the highest degree of stiffness” along two horizontal lines [49].

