### Study sample size calculation

Considering that the primary goal in this study is to improve clinical symptoms in the IF group compared to the normal diet (HAQ score is considered as the primary outcome in this study), the number of samples required to conduct this study based on the change in HAQ, the IF group compared to the usual diet by 0.68 (a minimum clinically important difference), and considering the test power of 80%, the type I error is equal to 0.05, and the standard deviation is 0.6 was calculated for the result of 20 people in each group. We used SPSS software for calculation.$$n=2\times \frac{{\left({z}_{1-\frac{\alpha }{2}}+{z}_{1-\beta}\right)}^2}{\Delta ^2}\ S2$$$${n}=2\times \left[{\left(1.96+0.84\right)}^2\times \right(\left(0/{6}^2\right)\Big]/{(0.68)}^2$$

*n* = sample size in each group

*a* = type I error = 0.05

*b* = Power = 0.80

*S*
^2^ = standard deviation of the studied result (SD)

Δ^2^ = minimal clinically important difference

Therefore, considering a 10% chance of dropping out, the final sample size will be 44 people (22 people in each group) [54].

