### Statistical analysis

Analyses will be performed according to the intention-to-treat analysis (ITT) method. Therefore, all participants who entered the study (regardless of whether they completed the 8-week study period) are included in the analysis. In people who will have a drop, the last data will be used. Then re-analyses will be performed based on the protocol-based analysis method (per protocol analysis), so that the changes in the results can be seen. Patients who finished the 8-week duration of the study and were visited by the researchers will be included in the per-protocol analysis. Descriptive and analytical statistics will be used for data analysis and all analyses will be done in SPSS version 24 software. The normal distribution of the variables will be checked through the scatter plot, histogram, and Shapiro-Wilk test. Variables with non-normal distribution will be reported as median (interquartile range). The mean (standard deviation) will be employed to quantify quantitative variables, while a frequency report (percentage) will be used to characterize qualitative variables. A comparison of absolute or relative frequency is done using the chi-square statistic. Between-group differences in trial results will be evaluated using a general linear mixed model for continuous variables and a chi-square test for categorical variables. Based on this, the significance will be defined in values of *P* less than 0.05 and *q* less than 0.1. Cohen’s changes will be calculated based on the mean and standard deviation, and based on that, the effect size (0.20, 0.50, and 0.80, respectively, low, medium, and high therapeutic effect) of dietary intervention will be determined. Also, a *P*-value < 0.05 will be considered statistically significant in all analyses.

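### The morning-stiffness duration options overlap, and if this item is the analysed outcome the plan's general rule gives it a chi-square test that ignores order and baseline

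*Protocol article*

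**What the plan says.** **The item.** Under Assessment of inflammation and pain, the protocol article gives five answers for stiffness duration: "less than 15 min, less than 30 min, less than 60 min, less than 90 min, and more than 90 min". It prints no instruction on which to choose when several apply.

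**A second measure.** The same paragraph adds a line scale for intensity: "The degree of perceived stiffness will also be determined by choosing on a scale of 0 to 10 cm".

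**The outcome.** Secondary outcomes lists "morning stiffness count (MS" among 14 measures, all defined as changes from baseline and assessed at the start of the intervention and 8 weeks later. It does not say which of the two measures MS is.

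**The test.** Statistical analysis gives one rule for between-group comparisons: "a general linear mixed model for continuous variables and a chi-square test for categorical variables". Morning stiffness is not named there, and no rank or ordinal method appears in the article.

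**The size.** From Study sample size calculation: "the final sample size will be 44 people (22 people in each group".

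**The concern.** There are two separate problems.

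*The options.* The first four are nested and there is a gap at 90 minutes. Two patients with the same stiffness could tick different boxes, and one patient could tick differently at baseline and at week 8 with no real change. The Randomization section says patients, doctors and researchers are not blinded, and the limitations paragraph accepts that subjective judgment may influence outcomes. A loosely worded self-report item is therefore undesirable here.

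*The test.* If the duration item is MS, it is an ordered five-level variable, and the stated rule gives it "a chi-square test for categorical variables". That test gives the same result if the five columns are shuffled, so it cannot use the fact that the hypothesis is a shift towards shorter stiffness. Applied to week-8 categories, it also leaves out the baseline answer, although the outcome is a change. Applied instead to the number of categories moved, it would use baseline, but it would still ignore order and would spread the patients over up to nine levels (-4 to +4).

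At stake is the chance of detecting a real shift in one secondary outcome, and the clean reading of its categories.

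**Working it through.** **1. Do the options partition the time scale?** Count the options that each duration satisfies as printed.

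| Duration | Options satisfied |
|---|---|
| 10 min | 4 (under 15, 30, 60, 90) |
| 20 min | 3 |
| 45 min | 2 |
| 75 min | 1 |
| 90 min | 0 |
| 100 min | 1 |

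They do not.

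**2. Inputs for the test comparison.** From the article: "with a 1:1 allocation ratio", 22 per arm randomised, 20 per arm before the dropout allowance, and "the type I error is equal to 0.05", two-sided because the sample size formula uses 1.96. The article states no power, distribution or effect for stiffness, so there is no figure of its own to reproduce. Assumed: a proportional-odds shift with odds ratio (OR) 1 to 8, and four control-arm distributions over the five categories:
- uniform: 0.20 each
- skewed short: 0.35, 0.30, 0.20, 0.10, 0.05
- centred: 0.10, 0.25, 0.30, 0.25, 0.10
- skewed long: 0.05, 0.10, 0.20, 0.30, 0.35

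**3. Analytic check on one case (uniform control, OR 3, 22 per arm).** Control cumulative odds are 0.25, 0.667, 1.5 and 4. Multiplied by 3 they are 0.75, 2, 4.5 and 12, so the treated-arm probabilities are 0.429, 0.238, 0.152, 0.105 and 0.077.

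Noncentrality of the Pearson test: λ = n Σ (p₀ − p₁)² / (p₀ + p₁) = 22 × (0.0831 + 0.0033 + 0.0067 + 0.0297 + 0.0547) = 22 × 0.1775 = 3.9.

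- On 4 degrees of freedom (critical value 9.49), λ = 3.9 gives power of about 31%.
- On 1 degree of freedom (critical value 3.84), the same λ gives about 51%.

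A rank test in effect puts a one-directional shift on 1 degree of freedom. The gap of about 20 points is the price of spreading it over 4.

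**4. Simulation.** 6,000 trials per scenario; Pearson chi-square (degrees of freedom = non-empty categories minus 1) against the tie-corrected Wilcoxon rank-sum test, on one set of post-treatment categories. With 22 per arm, ranges over the four distributions:

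| OR | Chi-square | Rank test | Difference (points) |
|---|---|---|---|
| 1 (no effect) | 3.7–4.8% | 5.0–5.4% | – |
| 2 | 11.5–13.5% | 23.4–24.7% | 10.8–12.2 |
| 3 | 26.1–30.1% | 48.5–52.0% | 21.9–23.1 |
| 4 | 39.5–46.1% | 65.1–70.5% | 24.4–26.4 |
| 5 | 51.5–59.4% | 77.0–82.2% | 22.8–25.5 |
| 6 | 60.5–70.7% | 83.8–89.4% | 18.7–23.3 |
| 8 | 72.6–83.7% | 91.7–96.0% | 12.3–19.0 |

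With 20 per arm, the differences for OR 2 to 8 run from 10.7 to 27.2 points. The uniform OR 3 row (30.1% and 52.0%) agrees with step 3.

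**5. Sparse cells.** 44 patients over 2 × 5 cells average 44/10 = 4.4 expected per cell. More than a fifth of expected counts were below 5 in 99–100% of simulated tables. Even so, chi-square rejected in only 3.6–4.8% of null trials at 20 or 22 per arm. Sparseness makes the test slightly conservative; it does not cause false positives.

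**The case against.** **The chi-square is not stated for this outcome.** A reader might infer that the plan tests morning stiffness with a chi-square. The article does not say so. It gives a rule by variable type, and the 0 to 10 cm scale, if that is MS, would go to the mixed model. The choice of test for one ordinal item is also a detail that a condensed article may leave to an analysis plan. This stands in part, and the point about the test must be conditional. But the rule as written covers every categorical variable and offers nothing for ordered ones, and the outcome list leaves the measure open.

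**A single figure for lost power.** A loss of about 20 points might be taken as a property of the plan. It is not: it comes from assumed odds ratios, and at OR 2 the loss is 11 to 12 points. The simulation also models neither change from baseline nor a baseline-adjusted analysis.

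**Sparse cells invalidate the test.** This is tempting with an average of 4.4 per cell, but type I error stays at or below nominal. The loss comes from ignoring order.

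**The better test would find the effect.** Not reliably. The rank test reaches only about half at OR 3 and a quarter at OR 2, because the trial was sized for HAQ.

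**Patients will pick the shortest option that applies.** Many probably will, and the actual form and its instructions are not shown. The article does not establish that misclassification will occur; the defect is in the wording as printed.

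**Conclusion.** The point holds in a limited form. On the text alone, the duration options overlap, leave 90 minutes uncovered, and the outcome list does not say which stiffness measure is MS. If MS is the duration item, the only stated test ignores order and, on week-8 categories, the baseline answer.

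The cost is then roughly 11 to 27 points of power against a rank test with 20 to 22 per arm. This rests on a proportional-odds shift of OR 2 to 8 and on assumed control distributions; none of these comes from the documents. There is no threat to type I error. This is one of 14 secondary outcomes, and the primary HAQ conclusion does not depend on it. It is worth correcting because the correction is cheap and the stated rule has a plainly better alternative.

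**What to change.** 1. State whether MS is the duration item or the 0 to 10 cm scale, or name both.
2. Analyse the duration item with an ordinal method instead of chi-square. A proportional-odds model with baseline category as covariate is preferable because it uses baseline; a Wilcoxon rank-sum test is the simpler alternative.
3. Treat the categories as under 15, 15 to under 30, 30 to under 60, 60 to under 90, and 90 minutes or more. If the form is not yet in use, reword it. If it is, leave it alone and prespecify that the shortest applicable option is recorded and that exactly 90 minutes goes to the top category.

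**Cost.** One sentence in the analysis section, one in the outcome definition, and one form line or coding rule; no new data. The model relies on approximately proportional odds. The article describes the trial as ongoing, so baseline and week-8 answers must be coded the same way; rewording the form midway could put them on different scales.

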### Blood sampling and biochemical measurements

Patients will be asked to fast for 10–12 h before having 10 cc of venous blood samples collected and then placed in the laboratory for 30 min to clot the blood, in a centrifuge with 3000 per minute for 10 min to separate the serum. The serum from the blood sample will be kept in a −80 °C freezer until the tests for measuring inflammatory factors are conducted, ensuring accurate results. Subsequently, the serum levels of CRP will be determined using the enzyme-linked immunosorbent assay (ELISA) method with the help of commercial kits. To measure ESR, the Wintergreen method will be used. In this method, the amount of 109 mmol per liter of trisodium citrate is combined with 4 ml of blood. The created mixture enters the 200 mm Westergren tube. After 60 min, the height of the transparent part of the tube is read, which is the ESR [50]. The total oxidant and antioxidant capacity will be measured using colorimetric methods with a microplate spectrophotometer (Microplate Spectrophotometer, USA Biotek). Total serum antioxidant capacity will be measured by the manual FRAP (Ferric reducing the ability of plasma) method. In this method, antioxidant compounds create colored complexes by reducing ferric ions to ferric ions. FRAP values are obtained by comparing the absorbance change at 593 nm. The stoichiometric factors of Trolox to measure the tested antioxidants including α-tocopherol, ascorbic acid, and uric acid are all 2.0, and bilirubin is considered 4.0 and will be expressed as a standard unit of Trolox (mmol Trolox equivalent/L) [51]. Evaluation of total oxidant status by a spectrophotometric method based on the oxidation of ferrous ion to ferric ion in the presence of oxidant substances such as hydrogen peroxide in an acidic environment and measurement of a ferric ion with the color of xylol orange with the maximum absorption at 560 nm and it will be expressed as μmol H2O2 Equiv./L [52]. The oxidative stress index will be calculated by dividing TOC by TAC [53].

### Study sample size calculation

Considering that the primary goal in this study is to improve clinical symptoms in the IF group compared to the normal diet (HAQ score is considered as the primary outcome in this study), the number of samples required to conduct this study based on the change in HAQ, the IF group compared to the usual diet by 0.68 (a minimum clinically important difference), and considering the test power of 80%, the type I error is equal to 0.05, and the standard deviation is 0.6 was calculated for the result of 20 people in each group. We used SPSS software for calculation.$$n=2\times \frac{{\left({z}_{1-\frac{\alpha }{2}}+{z}_{1-\beta}\right)}^2}{\Delta ^2}\ S2$$$${n}=2\times \left[{\left(1.96+0.84\right)}^2\times \right(\left(0/{6}^2\right)\Big]/{(0.68)}^2$$

*n* = sample size in each group

*a* = type I error = 0.05

*b* = Power = 0.80

*S*
^2^ = standard deviation of the studied result (SD)

Δ^2^ = minimal clinically important difference

Therefore, considering a 10% chance of dropping out, the final sample size will be 44 people (22 people in each group) [54].

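### The printed sample-size formula gives 13 per group (14 with the t distribution), not the stated 20, so the stated inputs, sample size and 80% power do not agree

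*Protocol article*

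**What the plan says.** All the inputs are in the section Study sample size calculation of the protocol article, except the allocation ratio, which is in Study design and participants.

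- Target difference in HAQ change, the primary outcome: "the IF group compared to the usual diet by 0.68 (a minimum clinically important difference".
- Power: "considering the test power of 80" per cent.
- Significance level: "the type I error is equal to 0.05", two-sided, since the formula uses z at 1 − α/2 and enters 1.96.
- Spread and result: "the standard deviation is 0.6 was calculated for the result of 20 people in each group".
- Allocation: "with a 1:1 allocation ratio".
- Final size: "considering a 10% chance of dropping out, the final sample size will be 44 people (22 people in each group".

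The section prints the usual two-sample formula and then the substitution, with 0.6 (typeset as 0/6) squared and divided by 0.68 squared. The key beneath describes S² as "standard deviation of the studied result (SD". The calculation is said to have been done in SPSS.

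**The concern.** The article gives the formula, every input and the result, so the result can be checked from the page, and it does not follow. The gap, 13 or 14 against 20 per group, is too large for rounding.

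This calculation is the only justification given for the size of the trial, and it concerns the primary outcome. As printed, a reader cannot tell whether the trial has clearly more power than stated or slightly less. Nor can the reader tell which HAQ difference the design can detect with 80% power, and that figure is needed to interpret a result that is not significant.

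**Working it through.** **Inputs.** Δ = 0.68, S = 0.6, z for two-sided α of 0.05 = 1.96, z for 80% power = 0.84, 1:1 allocation, 10% dropout. All are from the protocol article.

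**1. The printed formula with the printed inputs.**

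n = 2 × (1.96 + 0.84)² × S² / Δ² = 2 × 7.84 × 0.36 / 0.4624 = 12.21, so 13 per group.

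An exact two-sided t-test calculation gives 14 per group (power 79% at 13 and 82% at 14). The stated 20 is not reproduced.

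**2. Other methods at the stated α, power, SD and difference.** A one-sided test gives 10 (normal) or 11 (t). Allowing for a Mann-Whitney test, with efficiency 0.955 or 0.864, gives about 14 to 17. None gives 20.

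**3. Changes of input that come near 20.**

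| Change | n per group | Conflicts with |
|---|---|---|
| 0.6 entered unsquared as S² | 2 × 7.84 × 0.6 / 0.4624 = 20.35, strictly 21 | the stated SD and the printed square |
| α = 0.01 | 19 (normal), 20 (t) | the stated type I error |
| 95% power | 2 × (1.96 + 1.645)² × 0.36 / 0.4624 = 20.24, so 21 (22 with t) | the stated power |

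Each of these contradicts something the article states, so none can be taken as the calculation that was done.

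**4. What the planned size delivers under the two readings of 0.6.** Power is from the noncentral t distribution, with the normal approximation in brackets. If 0.6 is the variance, the SD is √0.6 = 0.775.

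| | 0.6 is the SD | 0.6 is the variance |
|---|---|---|
| Standardised difference | 0.68 / 0.6 = 1.13 | 0.68 / 0.775 = 0.88 |
| Power for 0.68, 20 per group | 93.7% (94.8%) | 77.2% (79.3%) |
| Power for 0.68, 22 per group | 95.7% (96.4%) | 81.2% (82.9%) |
| Difference detectable with 80% power, 20 per group | 0.55 (0.53) | 0.70 (0.69) |

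The normal-approximation detectable differences are 2.80 × SD × √(2/20): 2.80 × 0.6 × 0.316 = 0.53 and 2.80 × 0.775 × 0.316 = 0.69.

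**5. Dropout step.** 20 × 1.1 = 22 is what the article did. 20 / 0.9 = 22.2 would round up to 23, and 22 × 0.9 = 19.8. From the 13 or 14 that the printed inputs require, 13 / 0.9 and 14 / 0.9 round up to 15 and 16, both below the planned 22.

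**The case against.** The strongest defence is that nothing harmful follows. On the inputs as written, the error makes the trial larger than necessary. If 0.6 is the variance, the shortfall at 20 per group is 1 to 3 percentage points. The intention-to-treat analysis also counts everyone who entered, so with all 22 per group the power is about 81% even then. This stands as an argument about consequences: the trial is not put at risk, and a reader who infers that it is underpowered goes beyond the document. It does not make the printed calculation correct. Values carried forward for dropouts may dilute the effect, but that concerns the handling of missing data and not this arithmetic.

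Four stronger readings are tempting, and the article does not support them.

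- *That 0.6 was certainly entered as a variance.* It fits well, but it is an inference. The key's description of S² as an SD is weak evidence, because the same key labels Δ² as the difference itself and b as power. It is loose throughout.
- *That the dropout allowance is materially short.* The gap is 22 against 23 per group, or 19.8 against 20 evaluable. Measured against what the printed inputs require, 22 is more than enough.
- *That 0.68 conflicts with the effect-size bands in Statistical analysis* ("0.20, 0.50, and 0.80, respectively, low, medium, and high therapeutic effect"). Those bands describe observed effects and set no limit on the planning difference. A difference that matters on the HAQ scale may exceed 0.80 SD.
- *That 0.68 may not be called the minimum important difference.* Judging that needs the source of the figure, which is not shown.

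**Conclusion.** Wrong as written. The printed formula and inputs give 13 per group (14 with t), and 20 per group with 80% power does not follow from them. On the printed inputs the power at 20 per group is about 94%, and the difference detectable with 80% power is about 0.55. If 0.6 is the variance of HAQ change, the stated 80% is only approximate: about 77% at 20 per group and 81% at 22, with a detectable difference of about 0.70.

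These figures assume a two-sided comparison of two means with a common SD, equal groups and α of 0.05, as the article's formula does. The arithmetic of the mismatch is certain. Its cause is not, and only the source of the 0.6 and the software output can settle it. The point concerns the stated justification and does not call for a different trial size.

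**What to change.** Keep 44 patients. Check the source of the 0.6 and the SPSS run, state which inputs were used, and in particular say whether 0.6 is the SD or the variance of HAQ change. Then correct the formula, the key, n and the power together. The key should call S² the variance, Δ the difference, and 1 − β the power.

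- *If 0.6 is the SD:* 13 per group (14 with the t distribution) suffice for 80% power. The 20 evaluable per group give about 94% power for a difference of 0.68, or 80% power for about 0.55.
- *If 0.6 is the variance (SD 0.775):* remove the wording that calls 0.6 an SD and the square in the substitution. State that 20 evaluable per group give about 77% power (79% by normal approximation) and 22 give about 81%, with about 0.70 detectable with 80% power at 20 per group.
- *If the run used another α or power:* state those values and correct the text to match.

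The cost is one rewritten paragraph and no extra patients. Under the variance reading, the stated power at 20 per group becomes slightly less favourable.
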